## Abstract

**Background:**

Major Depressive Disorder (MDD) is a heterogenous brain disorder, with potentially multiple psychosocial and biological disease mechanisms. This is also a plausible explanation for why patients do not respond equally well to treatment with first- or second-line antidepressants, i.e., one-third to one-half of patients do not remit in response to first- or second-line treatment.

To map MDD heterogeneity and markers of treatment response to enable a precision medicine approach, we will acquire several possible predictive markers across several domains, e.g., psychosocial, biochemical, and neuroimaging.

**Methods:**

All patients are examined before receiving a standardised treatment package for adults aged 18–65 with first-episode depression in six public outpatient clinics in the Capital Region of Denmark. From this population, we will recruit a cohort of 800 patients for whom we will acquire clinical, cognitive, psychometric, and biological data. A subgroup (subcohort I, *n* = 600) will additionally provide neuroimaging data, i.e., Magnetic Resonance Imaging, and Electroencephalogram, and a subgroup of patients from subcohort I unmedicated at inclusion (subcohort II, *n* = 60) will also undergo a brain Positron Emission Tomography with the [^11^C]-UCB-J tracer binding to the presynaptic glycoprotein-SV2A. Subcohort allocation is based on eligibility and willingness to participate. The treatment package typically lasts six months.

Depression severity is assessed with the Quick Inventory of Depressive Symptomatology (QIDS) at baseline, and 6, 12 and 18 months after treatment initiation.

The primary outcome is remission (QIDS ≤ 5) and clinical improvement (≥ 50% reduction in QIDS) after 6 months. Secondary endpoints include remission at 12 and 18 months and %-change in QIDS, 10-item Symptom Checklist, 5-item WHO Well-Being Index, and modified Disability Scale from baseline through follow-up. We also assess psychotherapy and medication side-effects.

We will use machine learning to determine a combination of characteristics that best predict treatment outcomes and statistical models to investigate the association between individual measures and clinical outcomes.

We will assess associations between patient characteristics, treatment choices, and clinical outcomes using path analysis, enabling us to estimate the effect of treatment choices and timing on the clinical outcome.

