#### Baseline

##### Questionnaires

Questionnaires will be completed through a secure, web-based survey system hosted by the research centre so that participants can complete questionnaires electronically, either at home or during their visit to the research centre. Online questionnaires are sent via a national secure mail platform used by citizens in regular correspondence with public institutions and the health care system.

Measures include several salient domains in the clinical characterisation of the patient, among others, assessments of demographics (e.g., ethnicity, education, and marital status); medical and psychiatric history; depressive symptoms and impact of depression behaviour and day-to-day life; treatment preferences and expectations, life experiences; and a broad range of state and trait psychometrics. Some questionnaires will only be given to patients in subcohorts I-II (Table 2).

**Table 2 Tab2:** Questionaries Additional questionnaires for the subcohort I-II only are in bold

Symptom profile and Severity	Cognitive style	Upbringing and life history	Functioning and quality of life
Inventory of Depressive Symptomatology – self-report (IDS-SR) [34]	Mentalisation Questionnaire (MZQ) [35]	Online Stimulant and Family History Assessment Module (OS-FHAM) [11]	Cognitive Complaints in Bipolar Disorder Rating Assessment (COBRA) [36]
Dimension of Anger Reactions (DAR-5) [37]	Ruminative Response Scale (RRS) [38]	Child abuse and trauma scale (CATS) [39]	Modified Sheehan Disability Score (mSDS)
Generalised Anxiety Disorder 7-item (GAD-7) [40]	Perth Alexithymia Questionnaire (PAQ) [41]	**Parental Bonding Instrument (PBI)** [42]	WHO 5 wellbeing index (WHO-5)
Cohen's Perceived Stress Scale (PSS) [43]	**Mindful Attention Awareness Scale (MAAS)** [44]	**Stressful Life Events (SLE)** [45]	Changes in Sexual Functioning Questionnaire (CSFQ) [46]
Brief Symptom Inventory (BSI) [47]	**Short form of Metacognitions Questionnaire (MCQ-30)** [48]		Questions from the Copenhagen Aging and Midlife Biobank (CAMB) [49]
Symptom checklist (SCL-10) [50]	**Coping Self-Efficacy Scale (CSES)** [51]		Revised Sociosexual Orientation Inventory (SOI-R) [52]
Snaith-Hamilton Pleasure Scale (SHAPS) [53]			
**Pittsburgh Sleep Quality Index (PSQI)** [54]			

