##### Primary and secondary outcome measures

The primary clinical outcomes are categorical: *improvement* defined as ≥ 50% reduction in QIDS and *remission* after the treatment package defined as a QIDS ≤ 5. The secondary outcome is *change* in depression severity as measured by QIDS.

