##### Tertiary outcome measures

The ten-item depression and anxiety symptom checklist (SCL-10) [50, 71], well-being measured by WHO-5 [50, 72], and disability measured by a modified Sheehan Disability Scale (mSDS) are the established treatment effect parameters by the Mental Health Services of the Capital Region of Denmark.

Tertiary endpoints are three measurements of psychosocial remission defined as a WHO-5 score of > 49, an SCL-10 score of < 26 and an mSDS score of < 10. Additional tertiary clinical endpoints are changes in wellness (WHO-5), disability (mSDS), and symptomatology on the Brief Symptom Inventory 18 (BSI-18) and the SCL-10.

Two questionnaires assessing the negative effects of psychological and antidepressant treatment will be sent at the first follow-up, at the end of the treatment package. We use the Patient-Reported Inventory of Side-Effects (PRISE), originally developed and validated in Danish and also used in the STAR*D trial [71, 73]. The questionnaire is omitted if the patient has not been or is not on antidepressant medication. We use the short 20-item form of the Negative Effects Questionnaire (NEQ) to assess adverse and unwanted events in psychological treatment, i.e., new symptoms, dependency, stigma, hopelessness, and the experienced quality of treatment [74, 75]. Both baseline characteristics and treatment experiences, e.g., negative effects on the NEQ, will be used to investigate reasons for CBT and treatment package drop-out.

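### The abstract makes WHO-5 a secondary endpoint measured as percentage change; the Methods make it tertiary and measure plain change. The percentage version is the poorer choice, because it fails at a baseline of 0 and is unstable just above it.

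*Protocol article*

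**What the plan says.** The Methods paragraph of the abstract applies one percentage rule to four scales. After a percent sign, the secondary endpoints include "change in QIDS, 10-item Symptom Checklist, 5-item WHO Well-Being Index, and modified Disability Scale from baseline through follow-up".

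The body of the article differs. Under Primary and secondary outcome measures: "The secondary outcome is *change* in depression severity as measured by QIDS". No other scale is named there as secondary. Under Tertiary outcome measures, WHO-5 appears twice: as a dichotomy, one of "three measurements of psychosocial remission defined as a WHO-5 score of > 49" and the matching SCL-10 and mSDS cut-offs, and as a score: "Additional tertiary clinical endpoints are changes in wellness (WHO-5), disability (mSDS), and symptomatology". Neither mention has a percentage.

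WHO-5 is in the baseline questionnaire list (Table 2) and is repeated at 6, 12 and 18 months (Table 4). The article gives no WHO-5 range, no baseline mean or SD, and no rule for a zero or very low baseline.

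**The concern.** The four scales do not run the same way. The remission cut-offs show it: QIDS at most 5, SCL-10 below 26 and mSDS below 10, but WHO-5 above 49. On the first three, a more severely affected patient has a larger baseline and so a stable denominator. On WHO-5, the more severely affected patient has the smaller one. A ratio to baseline is then least reliable in the patients with most room to improve, and has no value if the baseline is 0.

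WHO-5 is one of three scales that the article calls established treatment-effect parameters of the regional mental health services. If the abstract's metric were carried into analysis, equal gains would be scored very differently, any patients at 0 would be lost in a way related to severity, and associations with baseline markers would be estimated less precisely than the data allow. Whether that happens depends on which of the two definitions governs, and the article leaves this open.

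**Working it through.** **No figure to reproduce.** The article's only power calculations concern the PET analyses. It states no power, SD or expected change for WHO-5.

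**Step 1: set the definitions side by side.**

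| Place | Tier of WHO-5 score | Metric |
|---|---|---|
| Abstract, Methods | secondary | percentage change from baseline |
| Primary and secondary outcome measures | not listed | – |
| Tertiary outcome measures | tertiary | change, no percentage; also above 49 |

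Tier and metric both conflict. SCL-10 and mSDS share the tier conflict.

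**Step 2: arithmetic of the percentage rule.** With baseline B and follow-up F, the rule is 100 × (F − B)/B. Assume a 0 to 100 score in steps of 4; this is not in the article but is compatible with the cut-off of 49. Three patients each gain 36 points:
- 0 to 36: 36/0, no value.
- 4 to 40: 36/4 = 9, so +900%.
- 24 to 60: 36/24 = 1.5, so +150%.

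Equal gains differ by 900/150 = 6 times. Likewise, reaching 52, just over the remission cut-off, is (52 − 4)/4 = +1200% from 4 but (52 − 48)/48 = about +8% from 48.

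**Step 3: size, by simulation.** From the article: 800 patients. Assumed: baseline normal with mean 16 to 36 and SD 10 to 16, rounded to steps of 4 and limited to 0 to 100; follow-up = mean + 22 + 0.4 × (baseline − mean) + 6 × marker + normal error with SD 20, rounded and limited in the same way; a binary marker with 50% prevalence, unrelated to baseline; two-sided 5% test; 400 replicates per scenario. The Monte Carlo standard error of a power near 50% is √(0.5 × 0.5/400) = 2.5 percentage points.

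| Quantity | Range over scenarios |
|---|---|
| No value (baseline 0) | 0 to 19% (up to 0.19 × 800 = 152 patients) |
| Share of percentage-change variance from baselines of 4 to 8 | about 22 to 78% |
| Power, mean-based test on percentage change | about 32 to 80% |
| Power, rank test on percentage change | about 69 to 92% |
| Power, unadjusted change in points | about 95 to 99% |
| Power, follow-up score adjusted for baseline | about 97 to 99% |

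In a middle scenario (mean 24, SD 12), 3.4% have no value (0.034 × 800 = 27 patients). Baselines of 4 to 8 make up 9% of the remaining patients but supply 72% of the variance. Power with the mean-based test on percentage change is roughly one half.

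**Step 4: a different baseline shape.** With a beta-shaped baseline, mean 12 to 36, SD 10 to 18, and a mean gain of 20 points (SD 20), the share at 0 runs from 0 to 44%. The variance share of baselines 4 to 8 runs from 2% (mean 36, SD 10) to 82% (mean 12). At mean 20, SD 15, the mean percentage change is 177% and the median 100%. On change in points in that scenario, patients at 8 or below supply 29% of the variance and are 31% of patients, so they count in proportion to their number.

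**The case against.** The strongest reply is that an abstract is a summary and the Methods govern. Read literally, the Methods already give change in points for WHO-5, and unadjusted change in points has about 95 to 99% power in the same model. On that reading most of the loss never arises. This largely stands: it is why the point is a conflict to reconcile and not a settled faulty derivation. It does not remove the point, because the percentage is the only explicit metric given for WHO-5 change, and the unqualified word in the Methods does not exclude it.

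Second, a reader might infer that depressed patients start near zero on WHO-5. The article does not say so. The cut-off of 49 shows the direction of the scale, not where patients begin.

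Third, a reader might infer that the lowest scorers decide the result. That depends on the assumed distribution: it fits low means or wide SDs, but not a mean of 36 with SD 10, where their variance share is 2 to 22% depending on shape. It also presumes a mean-based analysis. A rank test recovers much of the power, though it still has no value for a baseline of 0 and still ranks equal gains differently.

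Fourth, the Statistical analyses section promises more specific analysis plans before detailed analysis. The test, the summary measure and a rule for zero baselines may properly be set there, so their absence is no fault. Nothing in the article says that patients at 0 would be dropped.

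Last, where a hypothesis names an outcome scale, it is QIDS. This limits the importance of the point.

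**Conclusion.** The conflict between abstract and Methods on the tier and metric of WHO-5 is plain from the text and rests on no assumption. That percentage change is the poorer metric follows from the direction of the scale, which the article gives. That it has no value at a baseline of 0 needs the further assumption that the scale minimum is 0.

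The size is conditional. In the main simulation the direction is the same in every scenario: percentage change loses power against baseline-adjusted points. The loss ranges from moderate to large, and the share of patients without a value from none to about a fifth, according to a baseline distribution that the article does not state.

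The primary outcomes, QIDS remission and a reduction in QIDS of at least 50%, are not touched. Neither is the WHO-5 endpoint above 49. This is a minor-to-moderate improvement.

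**What to change.** 1. Reconcile the abstract with the two outcome sections: state once whether the WHO-5 score is secondary or tertiary, and in which metric. Settle the tier of SCL-10 and mSDS in the same edit.
2. Take WHO-5 out of the percentage rule. Analyse the score in points at 6, 12 and 18 months, adjusted for baseline WHO-5, including patients with a baseline of 0, and state that a positive difference is improvement.
3. Keep the endpoint above 49 as it is.

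The cost is about one sentence in the endpoint definition or the forthcoming analysis plan. No new data are needed, since baseline WHO-5 is already collected. The one drawback is that WHO-5 results no longer share a percentage metric with QIDS.

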**Discussion:**

The BrainDrugs-Depression study is a real-world deep-phenotyping clinical cohort study of first-episode MDD patients.

**Trial Registration:**

Registered at clinicaltrials.gov November 15th, 2022 (NCT05616559).

**Supplementary Information:**

The online version contains supplementary material available at 10.1186/s12888-023-04618-x.

## Background

Depression is the leading cause of disability worldwide, with an estimated 322 million people currently suffering from a depressive episode [1]. We know that pharmacotherapy and psychotherapy, individually or combined, can efficaciously treat Major Depressive Disorder (MDD) [2, 3].

Nevertheless, more than half of patients do not respond to the initial medication prescribed [4] and require sequential trials of different treatments that may not alleviate symptoms, resulting in treatment-resistant MDD [5, 6]. After the first depressive episode, approximately half of patients will experience a relapse or re-emergence of depressive symptoms [7]. Current treatment guidelines emphasise depression severity as the primary or exclusive element on which to base treatment choice [8]. Despite numerous studies on definitions, frequency, and determinants of relapse and treatment-resistant MDD [5, 9], we continue to lack clinically relevant markers to guide treatment choice in first-episode MDD.

MDD is highly heterogeneous, with complex disease mechanisms and diverse biological and psychological causes [10], complicating drug discovery and optimal patient care. Deep phenotyping with a subsequent analysis to stratify patients’ response to treatment is an essential tool to resolve this heterogeneity and move away from a ‘one-size-fits-all’ approach [11]. The prospect of this strategy is that patients instead can be stratified based on objective and replicable psychosocial, biochemical and/or neurobiological characteristics. Interventions would ideally be tailored to these individual profiles and thereby maximise clinical response [12]. Furthermore, precision medicine enables the optimisation of resource allocation within patient populations, e.g., by efficient allocation of relapse prevention and interventions to high-risk patient groups.

Previous studies have focused primarily on individual course predictors from just one or two domains, e.g., genetic [13], structural and functional neuroimaging [14–18], electroencephalographic biomarkers [19, 20], blood markers [21], cognitive disturbances [22, 23], and demographic or clinical data [24, 25]. So far, no single marker has proven reliable enough to be implemented in clinical practice [19, 26]. A multimodal approach to depression is essential as the disorder's aetiology is likely multi-causal. That is, prediction models that combine multiple candidate biomarkers might have more predictive utility [24], but must still be generalizable and cross-validated across different cohorts [27]. Other issues include small sample sizes, using data from randomised control trials, lack of clinically and biologically relevant predictive markers, short follow-up time, and poorly validated and biased prediction models [9, 26, 28].

So far, most studies have focused on predictors of response to pharmacological antidepressant treatment without examining the effect of other commonly used treatment modalities such as psychotherapy. Factors such as safety, tolerability, and the effect of the patient's preferences (e.g., dislike of medication or psychotherapy) on overall treatment outcome are also underexplored [26]. Together with substantial methodological variance across studies, these limitations have hampered the ability to draw ecologically relevant and generalizable conclusions from meta-analyses [26, 29, 30].

With this cohort-based study, we will generate a large longitudinal observational multi-modality clinical dataset that allows for a thorough analysis of which phenotypic components enable the best participant stratification for optimal treatment success. We will leverage the Danish healthcare system, which provides standardised treatment packages for all patients. Currently, group cognitive-behavioural therapy (CBT) constitutes the backbone of the treatment package with possibilities for initiation or changes in pharmacotherapy. The treatment package is nationally uniform and designed by Mental Health Services in the Capital Region. The treatment package was introduced in 2013 and revised in 2017 based on clinical and patient experience. However, while the treatment components in the package are research and evidence-based, the treatment effect in real life has not been examined.

The standardised treatment package system enables us to characterise newly diagnosed patients with depression and monitor their clinical response to different treatment modalities, combinations, and paths within the treatment package and deviations from it. Further, the individual Danish person identification number (CPR), combined with several national health and civil registers, will allow us to obtain additional information and follow the patients’ clinical progress longitudinally [31].

### Objectives

The primary objective of this study is to identify single or composite biomarkers that can reliably identify clinical profiles of MDD and predict their treatment outcomes.

To achieve this aim, we will establish a large, single-site cohort of adult patients diagnosed with first-episode MDD and referred for a treatment package for first-episode depression in secondary care, phenotyping patients before treatment initiation. All patients in the cohort (*n* = 800) will contribute with basic clinical, cognitive, psychometric, and biological data, i.e., genetics and blood biochemistry. A subcohort (subcohort I, *n* = 600) will provide Magnetic Resonance Imaging (MRI) and Electroencephalogram (EEG), and a second subcohort (subcohort II, *n* = 60) of subcohort I with patients unmedicated at inclusion will also undergo a Positron Emission Tomography (PET) brain scan with the presynaptic PET tracer [^11^C]-UCB-J. Clinical depression symptom severity is assessed with the Quick Inventory of Depressive Symptomatology (QIDS) at baseline (T_0_), and 6 (T_1_), 12 (T_2_) and 18 (T_3_) months after treatment initiation (Fig. 1). The treatment package typically lasts six months.

**Fig. 1 Fig1:**
[figure not shown]
Study design of the BrainDrugs-Depression prospective cohort. *QoL* Quality of life. Figure created by [name] with BioRender.com

To examine disease trajectories, we will combine collected data with information from Danish national health and social registers, allowing us to further characterise and follow the patients before, during, and after treatment. Together, this might enable us to identify clinically relevant biomarkers and suggest treatment response algorithms, aiding treatment choices and improving patient care (Figure 1).

Furthermore, synaptic loss and deficits in functional connectivity are hypothesized to contribute to depressive symptoms, i.e., cognitive dysfunction, anhedonia, and anxiety and treatment effect. Therefore, we will examine the relationship between presynaptic density and cognitive dysfunction, depressive symptoms, and treatment effect in antidepressant naïve patients (subcohort II) and compare their cerebral presynaptic density to healthy controls (HC).

### Hypotheses

#### The entire cohort

Primary hypotheses:1.1 Clinical, cognitive, psychometric, genetic, and blood biomarker measures at inclusion can predict clinical remission (defined as QIDS ≤ 5) at the first follow-up.1.2 Clinical, cognitive, psychometric, genetic, and blood biomarker measures at inclusion can predict clinical improvement (a ≥ 50% reduction in QIDS from pretreatment) at the first follow-up.

Secondary hypotheses:1.3 Composite scores across a range of clinical, cognitive, psychometric, genetic, and blood biomarker measures at inclusion can cluster patients into MDD subgroups associated with treatment trajectories and outcomes.1.4 Clinical, cognitive, psychometric, genetic, and blood biomarker measures at inclusion are associated with clinical outcome defined as a change in QIDS.1.5 Path analysis of baseline patient characteristics and treatment tracks can uncover causal paths for clinical improvements, i.e., estimate the effect of treatment on clinical outcomes.

#### Subcohort I

Primary hypotheses:2.1 MRI, fMRI, and EEG patterns at inclusion may be associated with depressive phenotypes.2.2 Adding EEG, MRI, and fMRI measures at inclusion to the classifier model (defined in hypotheses 1.1 and 1.2) may significantly improve the prediction of clinical remission and improvement.

Secondary hypotheses:2.3 Adding EEG, MRI, and fMRI measures at inclusion to the composite score (defined in hypothesis 1.3) may significantly improve the clustering of patients into MDD subgroups.

#### Subcohort II

Primary hypotheses:3.1 Cerebral [^11^C]-UCB-J binding is lower in patients with MDD than in healthy controls.3.2 Domain-specific cognitive function correlates positively with [^11^C]-UCB-J binding in associated cortical and subcortical areas.

Secondary hypotheses:3.3 Depression severity, anxiety, and anhedonia correlate with [^11^C]-UCB-J binding in associated cortical and subcortical areas.3.4 Addition of [^11^C]-UCB-J binding, EEG, and MRI measures at inclusion to the composite score (defined in hypotheses 2.1) can significantly improve the prediction of clinical improvement and remission beyond clinical, cognitive, psychometric, fluid biomarker, EEG, and MRI measures in antidepressant naïve patients.

